
**Fig. 4 Fig4:**
[figure not shown]
Assessment of underlying haemodynamic profile by MAP/HR ratio and the likelihood of vasoconstricted, low output or vasodilated high-output hypertension

### Outcome measures

#### Primary study endpoints

Severe hypertension, defined as a systolic blood pressure ≥ 160 mmHg and/or a diastolic blood pressure ≥ 110 mmHg [31].Preeclampsia defined as hypertension and one or more of the following new-onset conditions:
Proteinuria (spot urine protein/creatinine ≥30 g/mol or ≥ 300 mg/24 h);Renal insufficiency (creatinine levels ≥90 μmol/L);Liver involvement (elevated transaminases at least twice the upper limit of normal (≥70 U/I);Neurological complications (hyperreflexia when accompanied by clonus and/or severe headaches, persistent visual scotomata, altered mental status, eclampsia);Haematological complications (thrombocytopenia defined as platelet count below 150*10^9^/L, disseminated intravascular coagulation, haemolysis) [31].

#### Secondary and other study parameters

Maternal outcomes: side effects of medication, required level of care, serious maternal complications (maternal death, HELLP syndrome defined as the combination of thrombocytopenia, elevated transaminases and haemolysis, stroke, blindness, uncontrolled hypertension, respiratory failure, myocardial ischaemia/infarction, renal failure, hepatic haematoma and/or rupture, coagulopathy), birth-related variables, and placental abruption.

Neonatal outcomes: miscarriage, gestational age at delivery, birth weight and centile, Apgar score at 1 and 5 min after birth, use of antenatal corticosteroids and surfactant, adverse perinatal outcomes (miscarriage, stillbirth, neonatal mortality, and serious morbidity including neonatal sepsis, central nervous system morbidity and necrotizing enterocolitis), required level of care, and duration of care.

### Data collection

Data will be recorded in predesigned case record forms. Data on pregnancy and neonatal outcomes will be collected from the hospital maternity records. Additional neonatal outcomes will be collected from the discharge summary when neonates are admitted to the neonatal care department.

### Sample size / power calculation

Severe hypertension and preeclampsia develop respectively in 20% and 15–25% of women initially diagnosed with mild to moderate gestational hypertension [6, 32]. As severe hypertension and preeclampsia require comparable in-hospital treatment, we consider an 15% reduced incidence of both as clinically relevant. We calculated the sample size based on a progression level of 10% in the intervention group and a progression level of 25% in the control group. For a desired power of 80% and a two-tailed alpha level of 0.05, we need to recruit 99 women per group. Considering an anticipated dropout rate of 5%, we will recruit 208 women for randomization. We expect to include approximately 160 women who do not consent for randomization but agree to follow-up of their pregnancy outcomes. In this observational cohort, we will evaluate general obstetrical care for mild to moderate hypertension, patient characteristics, and patient outcomes comparable to the randomized population.

### Planned statistical analysis

The effectiveness of haemodynamically tailored treatment of mild to moderate gestational hypertension will be evaluated based on the intention-to-treat principle. Descriptive statistics will be used to compare baseline characteristics between study groups. The primary analysis will be an X^2^ test, or Fisher’s exact test in groups with less than five cases, to compare the incidence of severe hypertension and preeclampsia in the intervention group and the control group. We planned to conduct a per protocol sub-analysis in with women with at least 80% of their medication intake assessed by self-report at each pregnancy check-up. Secondary outcomes will be assessed by using X,^2^ Fisher’s exact test, Mann-Whitney U or T test as appropriate. For both primary and secondary outcomes, crude and adjusted odds ratio’s will be calculated (control group will be considerate as reference) and adjustments will be made for gestational age at recruitment. Separate analyses will be conducted to evaluate whether or not optimal blood pressure control was reached, if the type of medication and dosage affected the outcomes, which haemodynamic profiles were most prevalent, and if the initial haemodynamic profile affected the outcome, and to explore the effect of BMI, parity and age on the haemodynamic profile and response to medication.

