**Methods:**

Women diagnosed with mild to moderate hypertension without proteinuria or signs of other organ damage before 37 weeks of pregnancy are invited to participate in this randomized controlled trial. Women randomized to the intervention group will be prescribed tailored antihypertensive medication, using a simple diagnostic and treatment algorithm based on the mean arterial pressure/heart rate ratio, which serves as an easy-to-determine proxy for maternal circulatory state. Women randomized to the control group will receive non-pharmacological standard care according to national and international guidelines. In total, 208 women will be randomized in a 1:1 ratio. The primary outcome is progression to severe hypertension and preeclampsia and the secondary outcomes are adverse maternal and neonatal outcomes.

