**Fig. 3 Fig3:**
[figure not shown]
SPIRIT timetable of the study

Participants will be recruited from the outpatient clinic and department of obstetrics in Maastricht University Medical Centre, which is both a secondary and tertiary referring hospital. During every routine pregnancy check-up, blood pressure is measured. Women with mild to moderate hypertension (defined as systolic blood pressure measures ≥140 and < 160 mmHg and/or diastolic blood pressure ≥ 90 and < 110 mmHg) without symptoms or signs of preeclampsia will be given the study patient information form, and follow-up on blood pressure is planned at least 4 h later and within a few days. Eligible women who give consent will be randomized to the intervention or control group, after which they will continue regular pregnancy check-ups with blood pressure measurements; additional laboratory analysis will be performed as indicated. After 37 weeks’ gestation, induction of labour will be recommended to all participants, as this is associated with improved maternal outcome [27]. Study endpoints are an uneventful pregnancy and 6-week postpartum period, or diagnosis of severe hypertension or preeclampsia. In the latter case, participants will receive standard care, which usually means hospitalization and intensifying or initializing antihypertensive medication for the intervention group and control group, respectively.

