#### Exclusion criteria

Severe hypertension (systolic blood pressure ≥ 160 mmHg and/or diastolic blood pressure ≥ 110 mmHg);Diagnosed with preeclampsia, HELLP syndrome, or eclampsia;Taking antihypertensive drugs;Intending to terminate the pregnancy;Foetus has a major anomaly or chromosomal abnormality;Not able to comprehend the study outline;Contraindication for one of the possible prescribed antihypertensive medications.

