### Interventions

Eligible patients who consent to participate will be randomized to receive tailored antihypertensive medication (intervention group) or standard care (control group). The antihypertensive medications we plan to administer to participants in the intervention group can be safely prescribed to pregnant women [6]. Total peripheral vascular resistance (calculated as: 80 × MAP / cardiac output) indicates whether the hypertension is cardiac- or vascular-driven. In a healthy pregnancy, total peripheral vascular resistance drops from approximately 1300 to 1000 dyne.s/cm^5^ during the second and third trimester [28, 29]. Considering a standard deviation (SD) of 150 dyne.s/cm^5^, the upper limit of healthy dilated total peripheral vascular resistance is 1300 dyne.s/cm^5^. Women can be considered vasoconstricted when gestational vascular resistance exceeds 1300 dyne.s/cm^5^ and vasodilated when vascular resistance is below 1300 dyne.s/cm^5^. To avoid the need for an additional tool to assess cardiac output (stroke volume × HR), the MAP/HR ratio is used as a proxy for the haemodynamic profile. The MAP/HR ratio differs from total peripheral vascular resistance assessment in that it does not account for stroke volume. During healthy pregnancy, the mean ± SD stroke volume is 75 ± 10 ml. In the estimation of which proportion of women can be assumed to be vasoconstricted or vasodilated using the MAP/HR ratio, we can estimate the range in which total peripheral vascular resistance must be by taking the mean ± 2 SD stroke volume. When the MAP/HR ratio exceeds 1.4, more than 95% of all women must be considered vasoconstrictive. Contrary, when the MAP/HR ratio is 1.1 or less, more than 50% of women are likely to have a vasodilated circulation (Fig. 4). In the absence of empirical data that support the determination of cut-off values, we assumed a likelihood of more than 95% vasoconstrictive and relatively hypodynamic, corresponding a MAP/HR ratio 1.4 as reference value for considering vasodilating medication, and opposite, a likelihood of more than 50% of women to be vasodilated and hyperdynamic, corresponding MAP/HR ratio of 1.1 as a reference value for considering HR-lowering and with it, cardiac output-lowering medication. In the latter case, a beta-blocker with dual alpha- and beta-adrenergic receptor antagonism will account for the potential overlap in profiles. Thus, we will administer labetalol in the intervention group when hyperdynamic hypertension is assumed (MAP/HR ratio ≤ 1.1), and slow-release nifedipine when hypodynamic hypertension is assumed (MAP/HR ratio ≥ 1.4). Women with normodynamic hypertension will be identified by a MAP/HR ratio between 1.1 and 1.4 and will be prescribed methyldopa (Fig. 5). Treatment will be increased if the targeted blood pressure of < 130/80 mmHg (MAP 97 mmHg) is not achieved [7, 30]. The maximum dosages for blood pressure control are 800 mg three times daily for labetalol, 30 mg three times daily for slow release nifedipine and 1000 mg three times daily for methyldopa. If the maximum dosage has been administered and the MAP/HR ratio does not indicate another medication class, the blood pressure will be accepted. Moreover, in the unlikely event that blood pressure measurements fall below 95/50 mmHg, the treatment regime will be reduced and the last added medication step will be stopped. In case of intolerable side effects, the medication class will be switched; methyldopa will substitute labetalol or nifedipine, and nifedipine will substitute methyldopa when the MAP/HR ratio is ≥1.3 and labetalol when the MAP/HR ratio is < 1.3. Antihypertensive drugs will be provided by the local pharmacy. Since this is an open-label study, the participant, researcher, and physician will know the type and dosage of the prescribed medication. Adherence to the treatment and side effects of the medication in the intervention group will be discussed and recorded during each scheduled check-up.

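### The 80% intake rule for the per-protocol sub-analysis can apply only to the intervention arm, so that comparison loses the protection of randomisation and is open to bias of unknown size and direction

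*Protocol article*

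**What the plan says.** Under Planned statistical analysis, the article states that effectiveness "will be evaluated based on the intention-to-treat principle". It then adds a "per protocol sub-analysis in with women with at least 80% of their medication intake assessed by self-report at each pregnancy check-up". For the odds ratios of primary and secondary outcomes, the only covariate named is in this clause: "adjustments will be made for gestational age at recruitment".

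Four other places show who could have a medication intake to report:

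- Abstract, Methods: "Women randomized to the control group will receive non-pharmacological standard care according to national and international guidelines".
- Exclusion criteria: "Taking antihypertensive drugs" is a reason for exclusion, so no woman enters on a drug.
- Trial design and setting: once severe hypertension or preeclampsia is diagnosed, standard care usually means hospital admission and "intensifying or initializing antihypertensive medication for the intervention group and control group, respectively". Drug treatment of controls is therefore expected after the endpoint.
- Interventions: "Adherence to the treatment and side effects of the medication in the intervention group will be discussed and recorded during each scheduled check-up".

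**The concern.** A per-protocol set should be definable in both arms. Here the single stated criterion is a share of medication taken, and controls have none to take before the endpoint. The rule then either yields no control group or removes women from the intervention arm alone.

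Under the second reading, membership depends on behaviour after randomisation, reported by women who know their treatment. Interventions describes switching for intolerable side effects and escalation when the blood pressure target is missed, so the burden of the regimen may follow disease severity. Adherent women may therefore differ in prognosis from the full control group, and gestational age at recruitment would not capture that difference.

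This is the only analysis framed as the between-arm effect in women who take the treatment. If it departs from the intention-to-treat result, a reader could not tell a drug effect from selection.

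**Working it through.** **1. Which arm can the rule select in?** Controls have non-pharmacological care, no drug at entry, drug expected only at the endpoint, and no stated recording of adherence. Intervention women have drug from allocation and adherence recorded at each check-up. The rule can select only in the intervention arm.

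**2. Inputs from the article.** The sample size section gives 25% progression in controls, 10% in the intervention group (a planned 15-point difference) and 99 women per group. The 99 is reproduced closely:

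- unpooled: (1.960 + 0.842)² × (0.25×0.75 + 0.10×0.90) / 0.15² = 96.8
- pooled variance: 99.5

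Nothing below turns on that figure.

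**3. Assumed inputs.** The article gives no adherence rate and no risk by adherence. Suppose the drug has no effect and true risk is 25% in both arms. Let a be the adherent share and r the risk in non-adherers relative to adherers. Then a·pA + (1 − a)·r·pA = 0.25, so pA = 0.25 / [a + (1 − a)r].

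The comparison is 99a adherent women with 99 controls. With d = 0.25 − pA, SE0 the pooled and SE1 the unpooled standard error, the chance that a two-sided 5% test rejects is Φ[(d − 1.96·SE0)/SE1] + Φ[(−d − 1.96·SE0)/SE1].

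Example, a = 0.80 and r = 2:

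- pA = 0.25/1.20 = 20.8%, so d = 4.2 points
- SE0 = 0.0636, SE1 = 0.0631
- rejection = 0.094 + 0.004 = 9.8%

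Each cell gives the adherers' risk, the spurious difference in points, and the rejection rate:

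| a | r = 1.5 | r = 2 | r = 3 |
|---|---|---|---|
| 90% | 23.8%; −1.2; 5.4% | 22.7%; −2.3; 6.5% | 20.8%; −4.2; 10.3% |
| 80% | 22.7%; −2.3; 6.3% | 20.8%; −4.2; 9.8% | 17.9%; −7.1; 20.5% |
| 70% | 21.7%; −3.3; 7.6% | 19.2%; −5.8; 13.8% | 15.6%; −9.4; 30.4% |
| 60% | 20.8%; −4.2; 8.8% | 17.9%; −7.1; 17.3% | 13.9%; −11.1; 37.7% |

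With r = 1 there is no bias. With r below 1 the sign reverses: a = 0.80 and r = 0.5 give 0.25/0.90 = 27.8%, a spurious harm of 2.8 points.

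**4. A second route.** Let risk = expit(−1.315 + x) with x standard normal (marginal risk 25%, AUC 0.74) and adherence = expit(1 − kx). Numerical integration gives:

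- k = 0.5: 72% adherent, 22.8% events in adherers, difference −2.2 points, rejection 6.2%
- k = 1.0: 70% adherent, 20.7% events in adherers, difference −4.3 points, rejection 9.7%
- k = −0.5: 27.0% events in adherers, so the bias runs against treatment

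**5. Why the replacement should not keep the 80% cut.** An instrumental-variable estimate with exposure set to 1 at 80% intake treats a woman taking 70% as untreated. If partial takers benefit equally, the intention-to-treat difference is the planned 15 points, 70% reach the cut and no control is treated, the estimate is 15/0.70 = 21.4 points. That overstates the effect by 6.4 points, more than the roughly 2 to 4 points of selection bias in step 4.

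**The case against.** The strongest reply is that little hangs on this. The article evaluates effectiveness by intention to treat and calls the per-protocol work a sub-analysis, and the sample size does not rest on it. That stands, and it limits the weight of the point.

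A second reply is that a journal article may leave control-arm criteria to the full protocol or SAP. This stands in part. It would be wrong to infer that controls who start a drug early are nowhere handled: intention to treat keeps them in their arm, and a fuller document may define a criterion. But the article does state the rule, the threshold and the measurement. A matching control criterion would supply a comparator, yet the treated arm would still be chosen on behaviour after randomisation.

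A reader might also infer that the sub-analysis is biased, and towards benefit. The documents do not support this. They give no adherence rate and no relation between adherence and risk. One mechanism may run the other way: 80% is a proportion, and a short record before early progression may be easier to keep above it, which would place early events among adherers.

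Finally, the article also plans separate analyses of medication type, dosage and blood pressure control, so this is not its only look at treatment received.

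**Conclusion.** The point holds as a defect in a stated rule. The 80% criterion cannot be applied to controls, so the sub-analysis has either no comparator or one selected differently from the treated group. Under the natural reading it is open to bias of unknown size and direction.

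The illustrative size, always with no drug effect and 25% risk in both arms, is about 2 to 4 points if adherence falls with a moderately predictive risk factor. It is about 1 to 11 points if 60% to 90% adhere and non-adherers have 1.5 to 3 times the adherers' risk. The nominal 5% test then rejects 5.4% to 37.7% of the time. These ranges rest wholly on assumed links; at zero association the bias vanishes, and with the opposite association it reverses.

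It should not be read as a threat to the trial's main conclusion: the primary intention-to-treat comparison is untouched. The change is worth making before analysis, but it concerns a supportive result.

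**What to change.** Make the supportive estimate of the effect of taking treatment a complier-average effect in all randomised women, with allocation as the instrument: the intention-to-treat risk difference divided by the between-arm difference in exposure, with a bootstrap or two-stage least squares interval. Define exposure the same way in both arms, in one of two forms:

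- any antihypertensive started before a primary event; or
- proportion of intake as a continuous exposure.

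Neither form assumes that women below 80% get no effect. The estimate is null whenever the intention-to-treat difference is null.

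If the 80% subset is still shown, state a matching criterion for controls (no antihypertensive before the endpoint), label the result exploratory and draw no efficacy conclusion from it.

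The cost is SAP wording, one analysis, and the date of any antihypertensive start in controls. The limits should be stated:

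- The interval is wider, and the continuous form still relies on self-reported intake and assumes that the effect is proportional to it.
- The any-start form will lie close to the intention-to-treat result if nearly all intervention women start.
- Exposure counted only before an event is cut short in women who progress early.
- The method assumes that allocation acts only through treatment, which is imperfect in an open-label trial.

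### In the intervention arm, the planned drug-type and dose analyses cannot separate first drug from haemodynamic profile, or dose from disease severity, and should be descriptive only

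*Protocol article*

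**What the plan says.** The Interventions section assigns the first drug in the intervention arm by MAP/HR: labetalol at 1.1 or below, slow-release nifedipine at 1.4 or above, and for the middle group "Women with normodynamic hypertension will be identified by a MAP/HR ratio between 1.1 and 1.4 and will be prescribed methyldopa". Treatment is stepped up when the blood pressure target is missed. At the top of the range, "If the maximum dosage has been administered and the MAP/HR ratio does not indicate another medication class, the blood pressure will be accepted". The class may be changed for intolerable side effects, and the two worked examples show a second class being added according to the ratio at that visit.

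The Planned statistical analysis section lists several separate analyses after the primary and secondary comparisons. One asks "if the type of medication and dosage affected the outcomes". Another is to "evaluate whether or not optimal blood pressure control was reached". A third looks at the effect of the initial haemodynamic profile on outcome, without saying whether this is a comparison of the randomised arms within profile. The only adjustment stated in the section, for the primary and secondary outcomes, is for gestational age at recruitment.

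**The concern.** The protocol's Background treats the profile as prognostic: it links high vascular resistance to earlier maternal disease and poorer foetal growth, and a hyperdynamic circulation to later disease and normal growth. If first drug is a function of profile, women starting on nifedipine and women starting on labetalol are expected to differ in outcome even if the drugs are equivalent. Adjustment cannot repair this, because no profile contains both first drugs.

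Dose raises a similar problem. It goes up when blood pressure does not respond, so a high dose partly marks resistant disease. Adjusting for gestational age at recruitment addresses neither problem.

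At stake is a published statement that a drug or a dose helped or harmed in pregnancy, when the data may only reflect which women were given it. Meanwhile the comparison that randomisation does protect, intervention versus control by baseline MAP/HR, is not spelled out.

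**Working it through.** **1. Structure of the allocation (Interventions section).**

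| Baseline MAP/HR | First drug in the intervention arm | Other first drugs in the same band |
|---|---|---|
| ≤ 1.1 | labetalol | none |
| between 1.1 and 1.4 | methyldopa | none |
| ≥ 1.4 | nifedipine | none |

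Within this arm, first drug and profile band are one variable. A model with both has no information to separate them. Added classes and side-effect switches create some variation, but they follow blood pressure, the current ratio or intolerance, and none is randomised.

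**2. The plan's own sample size.** Inputs from the Sample size / power calculation section: assumed progression of 10% with intervention and 25% with control, 80% power, two-sided alpha 0.05. The stated result is "we need to recruit 99 women per group".

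n = [1.96·√(2·0.175·0.825) + 0.8416·√(0.10·0.90 + 0.25·0.75)]² / 0.15² = 99.5 per group.

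This reproduces the stated 99 to within rounding (power at 99 per group is 79.8%).

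**3. Size of the bias when there is no drug or dose effect.** The documents do not give risks by profile or the link between severity and escalation, so these are assumptions. Each scenario used 400,000 simulated women, three equally common profiles, 1:1 arms and severity S ~ N(0,1). The event log-odds were logit(profile risk) + b·S, with no treatment term. High dose was S + 0.7·N(0,1) > 0.5, and control reached was S + 0.7·N(0,1) < 0. The profile risks listed are those at S = 0.

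| Assumed profile risks | b | OR nifedipine v labetalol | OR high v low dose | OR control reached v not | OR intervention v control, by profile |
|---|---|---|---|---|---|
| 10/25/40% | 0 | 5.94 | 0.98 | 1.02 | 0.99–1.00 |
| 10/25/40% | 0.5 | 5.44 | 1.86 | 0.55 | 0.99–1.02 |
| 10/25/40% | 1.0 | 4.60 | 3.02 | 0.33 | 1.00–1.01 |
| 20/25/30% | 0.5 | 1.66 | 1.87 | 0.54 | 0.97–0.99 |

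The true odds ratio is 1 in every cell. The drug and dose columns depart from 1 by amounts that depend wholly on the assumptions. The randomised contrast within profile stays at about 1 throughout.

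The simulation lets escalation follow severity only. It does not model the fact that reaching the endpoint moves a woman to standard care (Trial design and setting). That would leave early progressors at low study doses and push the dose association the other way.

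**4. Precision of the randomised contrast within profile.** Profile prevalence is not given. Equal thirds of 99 give 33 per arm, and equal thirds of 104 give about 35.

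- Half-width of the 95% interval for 25% v 10%: 1.96·√[(0.25·0.75 + 0.10·0.90)/n]. At n = 33 this is 0.180, at n = 35 it is 0.175, and at n = 50 it is 0.146.
- Power for 25% v 10% within one profile: 23% at 20 per arm, 36% at 33, 51% at 50, 58% at 60.
- Interaction between two profiles (15 points in one, none in the other): at 33 per arm the SE is √[(3·0.1875 + 0.09)/33] = 0.141. Power is Φ(0.15/0.141 − 1.96), about 19%. At 50 per arm it is about 26%.

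**The case against.** The best case for the plan is that these are secondary, exploratory questions. The trial's objective is the tailored strategy against standard care, and the intention-to-treat comparison answers that. This stands, and it limits the weight of the point.

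Several stronger readings are tempting but not supported:

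- **That all drug comparisons are fully confounded.** This is exact for the first drug only. Later additions and switches are not clean comparisons, but they are not perfectly aliased with profile.
- **That the analyses will show more drug causing more progression.** The gradient depends on a severity effect the documents do not give. It vanishes when that effect is zero, and it could reverse because progression ends study titration.
- **That the blood pressure control item is a responder comparison.** As worded it asks whether control was reached, which is description. The objection applies only if control status is then related to outcome.
- **That no planned analysis uses the control arm.** The profile analysis is not restricted to one arm, so stating it as a randomised contrast is partly a clarification.
- **That the randomised contrast costs nothing.** It needs baseline heart rate in controls, which the article implies is routinely available but does not say is recorded, and its precision is poor.

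It is also fair to say that the contrast within profile does not remove the aliasing. It compares tailored treatment with standard care in that profile and cannot say which drug or dose is better.

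What survives is that the article states an effect question about drug type and dose which its own treatment algorithm prevents it from answering. That concerns what is written, so it is not a detail left to an analysis plan.

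**Conclusion.** The point holds in this limited form. For the first drug, inseparability from baseline profile follows directly from the protocol and needs no assumption. For dose, confounding by blood pressure response is built into the escalation rule, but its size is unknown and its direction uncertain. The simulated odds ratios (1.7 to 5.9 for drug, about 1 to 3.0 for dose) show what is possible under assumed profile and severity effects; they do not forecast this trial. The comparison of randomised arms by baseline MAP/HR is free of this bias, though randomisation was not stratified by profile. At roughly ±17 to 18 points, 36% power per profile and 19% power for a two-profile interaction, all assuming equal thirds, it can only be exploratory. The sample size and the primary conclusion are untouched.

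**What to change.** Change the wording of the separate analyses; no treatment rule is affected.

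1. Report outcomes by drug type and by dose as description, with no effect claim. Do the same for blood pressure control reached if it is set against outcome.
2. Confirm that MAP and heart rate at randomisation are recorded in both arms.
3. State the profile analysis as an exploratory randomised contrast: intervention versus control by baseline MAP/HR, with an arm-by-MAP/HR interaction. Use the ratio as a continuous variable, show the protocol's three bands for display, and give confidence intervals throughout.
4. Say in the report that this contrast estimates tailored strategy versus standard care within a profile, not the merit of one drug or dose over another.

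The cost is a few lines of text and, if it is not already collected, one heart rate reading at inclusion for each control. The drawback is wide intervals, so a null interaction should not be read as evidence that profile does not matter.
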